### Participants

Inclusion criteria for *perinatal intervention participants* include (1) 16 years of age or greater; (2) Identify as Latina; (3) Speaks Spanish/prefers to receive services in Spanish; (4) Pregnant or have a child 9 months or younger; At risk for a major depressive episode based on the following: mild to moderate depressive symptoms [5–14] on the Edinburgh Postnatal Depression Scale [52] and/or presence of risk factors for Major Depressive Episode (MDE) onset as measured by the Postpartum Depression Predictors Index-Revised (PDPI-R) [53–55]; ≥ 3 on PDPI-R when administered prenatally or ≥ 4 on the PDPI-R postnatally, or history of depression as indicated on the PDPI-R, regardless of score). Study exclusion criteria include (1) Individuals who score > 14 on the EPDS (likely meet criteria for a current major depressive episode for whom treatment would be recommended (vs. preventive intervention for depression); (2) Individuals who are not at risk for PPD—i.e., scores < 5 on the EPDS and under the aforementioned cutoffs on the PDPI-R and no personal history of depression; (3) Staff concern about cognitive limitations of a potential participant such that there is concern that they would not understand the intervention material; (4) Staff concern about a potential participant’s capacity to engage in a group intervention (e.g., concern about disruptive behavior); and (5) Unable to speak and understand Spanish.

As part of exploratory analyses, we will recruit *children of perinatal study participants* who are between the ages of 2.5 and 4.5 years at baseline. Inclusion criteria for intervention facilitators/staff and Judy Center directors include that the staff is a facilitator or co-facilitator of MB-VG groups or a director at a site participating in the study (either referring participants or delivering via their site). We plan to enroll a total of 486 study participants: (1) 300 perinatal individuals, (2) 150 children of perinatal individuals, (3) 24 MB-VG facilitators, and (4) 12 Judy Center directors.

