### Virtual observations

Related to our exploratory aim, participants with a child aged 2 ½–4 ½ will be invited to complete a virtual Zoom observation at the 6-month post-intervention time point after they complete their SCID. Observations will be video recorded to facilitate coding, with coded data entered into REDCap for analysis. Based on 2020 Judy Center data, we anticipate ~ 50% of families (*n* = 150) will have a child aged 2 ½–4 ½, who will provide data for this exploratory aim. Participants who complete virtual observations will be compensated $20.

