### Statistical analysis

Power calculations were conducted focusing on the effectiveness aim using maternal self-report of depressive symptoms (measured by the Center for Epidemiologic Studies-Depression scale (CES-D)) and parenting practices (measured by the Parental Cognition and Conduct Towards the Infant Scale (PACOTIS)), assuming power = 80%, a two-tailed test with an alpha of 0.05. To do these power calculations, we used the PowerUp tool. We plan to recruit 300 participants for the trial, 150 participants per condition. Based on these numbers, we expect a minimal detectable effect size of 0.241. Because of the longitudinal nature of the study, we expect some attrition (~ 20%). Accounting for attrition, we can expect a minimal detectable effect size of 0.269. Based on prior research, we expect small to moderate effect sizes, which we will have the ability to detect. We believe clustering by group will be very small and thus do not take it into account in the power analysis. Doing so would lead to a small increase in the minimal detectable effect sizes (e.g., increasing from 0.241 to 0.284).

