### Missing data

Sample size and power calculations were completed under the assumption of 20% attrition for primary outcome analyses. Thus, while we anticipate missing data, we still expect adequate power to detect differences between study arms. We will examine rates of missing data for all variables and determine whether rates vary by participant characteristics, Judy Center program, or study arm. These analyses will indicate the extent to which missing data could bias results. We will attempt to collect data at each time point regardless of participants’ engagement in earlier data collection efforts. To minimize missing data due to loss to follow-up, we will devote considerable attention to promoting study retention. The planned mixed effects models are generally robust for unbalanced data across study time points. However, we plan to apply multiple imputation to test for bias introduced by missing data in sensitivity analyses; we will impute at least five datasets to generate an estimated average intervention effect.

We plan to perform all analyses using both the intent-to-treat (ITT) approach and a dose–response approach (treating dosage as a continuous variable of 0–10 sessions attended), adjusted for propensity scores. The dose–response approach will examine the relationship between number of MB-VG sessions attended (dosage) and outcomes, using propensity scores to match intervention participants to control-group participants with a similar propensity to take up a given level of intervention. This will reduce the influence of self-selection bias in intervention take up on the estimates of dosage effects. We plan to stratify analyses by whether participants are prenatal vs postpartum and whether participants are primiparous or multiparous.

Interim analysis will be performed to ensure safety. This analysis will focus on whether participating in the intervention has any significant iatrogenic effects. Individuals who score > 40 on the CES-D at any assessment timepoint will be flagged, since this level of symptomatology can be considered “very severe”; these participants will be contacted by the research team per procedures described below in the " Safety considerations and procedures" section. The safety analysis dataset will include those participants who had at least one session of the study intervention. No other formal planned interim analyses are planned.

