*Effectiveness outcomes*: Aim 1 will be tested by examining the coefficient of the treatment vs. control indicator in the random effects model. We will include random intercepts for group and instructors and will also investigate whether a random slope for group is appropriate for the intervention effect. Intervention group, covariates measured at pretest (especially the pretest measures of the outcome, as available), the Judy Center the participant was recruited from, and instructor characteristics will be included as fixed effects. Likelihood ratio tests (significance criterion, *p* < 0.05) will be used to simplify the models following a backward selection strategy. Although the primary analyses will consider each set of follow-up outcomes separately, controlling for pre-test measures in each analysis, we will also consider the use of longitudinal growth models to model the growth in knowledge over the three time points. Primary endpoint #1 is depressive symptoms, as measured by the Center for Epidemiologic Studies-Depression scale (CES-D). A total continuous score (0–60) is calculated for the CES-D. Primary endpoint #2 is depressive episodes as measured by the SCID. The SCID is used to assess the presence/absence of major depression, making it a binary outcome (yes/no). Primary endpoints #3 and #4 are parenting self-efficacy measured via the PACOTIS and parenting responsiveness measured via the MIRI and PCOS (used as a separate coding system when coding the DB-DOS observation assessment). A mean score is calculated for each of the PACOTIS and MIRI subscales. Secondary endpoint #1 is anxiety symptoms, measured via the GAD-7. A total continuous score is calculated for the GAD-7. Secondary endpoint #2 is perceived stress, measured via the PSS-10. A total continuous score is calculated for the PSS-10.

Covariates will be finalized in a Statistical Analysis Plan but based on our prior studies [80, 87] will include (1) whether participant is a first-time mother (e.g., current number of children = 0 at baseline; (2) education (at least some high school vs less than high school); (3) mental health service utilization (we will control for enrollment with a therapist for counseling at baseline and medication for depression at baseline).

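### The example coding of first-time mother as zero children at baseline cannot identify first-time mothers who enrol postpartum, so it mixes parity with perinatal stage

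*Protocol article*

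**What the plan says.** Three places in the protocol article bear on this point.

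- **Quantitative analysis**, paragraph on covariates. The first covariate is "whether participant is a first-time mother (e.g., current number of children = 0 at baseline". The list is provisional: "Covariates will be finalized in a Statistical Analysis Plan".
- **Participants**, inclusion criterion 4. A woman qualifies if "Pregnant or have a child 9 months or younger", so there are two routes of entry, before and after delivery.
- **Missing data**, second paragraph. Analyses are to be stratified by "whether participants are prenatal vs postpartum and whether participants are primiparous or multiparous". These are two separate factors, and the article gives no definition of primiparous there or elsewhere.

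Nothing in the article adapts the zero-children rule to women who enrol after delivery.

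**The concern.** The covariate is meant to capture whether this is the woman's first child. Counting current children does that only for women who are still pregnant. After delivery the index infant is itself a child, so the count is at least one for everyone and the rule can never return first-time.

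Four things are at stake, in falling order of certainty.

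- The covariate no longer means what its label says. Its zero category pools experienced mothers with postpartum first-time mothers.
- Some of the precision that parity could bring is lost. Parenting self-efficacy and responsiveness are among the primary endpoints, and first-time status is plausibly prognostic for both.
- Models are to be simplified by backward selection with likelihood ratio tests at p < 0.05. A miscoded term may be kept or dropped for reasons unrelated to parity.
- If the SAP copies the only definition available into the parity strata, those strata are damaged in a way that affects interpretation as well as precision.

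**Working it through.** The article states no figure for this covariate, so there is none to reproduce. The check is logical, followed by an illustration of size.

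**Step 1. The rule against the entry criterion.**

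| True status at baseline | Current children | Coded by the rule |
|---|---|---|
| Pregnant, no earlier child | 0 | first-time (correct) |
| Pregnant, earlier child | 1 or more | not first-time (correct) |
| Postpartum, index infant is the first | 1 or more | not first-time (**wrong**) |
| Postpartum, earlier child as well | 2 or more | not first-time (correct) |

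The error is confined to one row, and there it affects 100% of women. It runs one way: every woman coded first-time is one. The variable is therefore pregnant AND no child.

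**Step 2. How many women.** The sample size is in the article: "We plan to recruit 300 participants for the trial, 150 participants per condition". The shares needed are not, so they are assumptions.

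Miscoded = 300 × (share enrolling postpartum) × (share of those who are first-time mothers)

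- Low: 300 × 0.40 × 0.30 = 36 (12% of the sample)
- High: 300 × 0.60 × 0.50 = 90 (30%)

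The article offers one partial bound. Under Virtual observations, "we anticipate ~ 50% of families" will have a child aged 2½ to 4½, so first-time mothers can be at most about half of all participants. The high figure sits at that ceiling and is generous, because it leaves no room for mothers whose older children fall outside that age band.

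A wider grid takes an overall first-time share f of 0.2 to 0.5 and a pregnant share g of 0.3 to 0.7, assumed independent. Miscoded = 300 × f × (1 − g), which runs from 300 × 0.2 × 0.3 = 18 to 300 × 0.5 × 0.7 = 105.

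**Step 3. What the variable tracks.** With c = fg the share coded first-time, the correlations with true first-time status and with pregnancy are

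- φ(coded, first-time) = (c − cf) / √[c(1 − c) f(1 − f)]
- φ(coded, pregnant) = (c − cg) / √[c(1 − c) g(1 − g)]

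At f = 0.4, g = 0.5: c = 0.20, so φ = 0.12/√(0.16 × 0.24) = 0.61 with first-time status and 0.10/√(0.16 × 0.25) = 0.50 with pregnancy. Over the grid the ranges are 0.42–0.81 and 0.26–0.64. Of the 12 combinations, first-time status has the higher correlation in 8, the two tie in 2 (where f = g), and pregnancy is higher in 2 (where g is below f). Only 20–50% of pregnant women are coded first-time.

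**Step 4. If the coding were reused for the strata.** At f = 0.4, g = 0.5 the 300 women divide as follows.

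| | True first-time | True experienced | Coded first-time | Coded not first-time |
|---|---|---|---|---|
| Pregnant | 60 | 90 | 60 | 90 |
| Postpartum | 60 | 90 | 0 | 150 |

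The postpartum primiparous cell is empty whatever the shares. In this example the coded multiparous stratum holds 90 + 150 = 240 women, of whom 60 (25%) are first-time mothers. Effect modification by parity could not be examined after delivery, and overall it would be mixed with perinatal stage.

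**The case against.** The best defence is that nothing is locked. The construct named, being a first-time mother, is right. Only the parenthetical is faulty; it is introduced as an example, and the covariates are to be settled in an SAP that is not shown. That stands, and it limits the weight of the point. It does not remove it: this is not detail left out but the only definition the article offers, it fails for one of the two entry routes, and an SAP author would naturally copy it.

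Three stronger readings are tempting, and the documents support none of them.

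- *A reader might infer that the covariate becomes a proxy for being pregnant.* It does not. Pregnant women with older children are coded not first-time, together with all postpartum women, and in most of the assumed scenarios the variable follows true first-time status more closely than pregnancy.
- *A reader might infer that the treatment effect is biased.* This is a baseline covariate in an individually randomised comparison. Miscoding it does not bias the intention-to-treat effect. The precision loss cannot be sized from the article and may be small, since baseline values of the outcome are given priority among the covariates.
- *A reader might infer that the parity strata are already compromised.* The stratification is described in different words in another section, without reference to the covariate rule, and beside a separate prenatal/postpartum factor. Harm there is conditional on reuse.

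It is also fair to object that the counts of women rest on assumed shares and measure misclassification, not any change in a result.

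**Conclusion.** The point holds as a faulty example definition. Read literally, the zero-children rule codes all postpartum first-time mothers as not first-time; that follows from the entry criterion alone and needs no assumption. The count is uncertain: 36–90 of 300 under the first pair of assumed ranges, 18–105 under the wider ones.

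For the main intention-to-treat comparison the consequence is modest: some lost precision and a coefficient that is hard to interpret. For the parity strata it would be serious only if the coding were carried over, and the article does not say that it will be. The article also does not say whether this covariate enters the propensity scores of the dose–response analysis, so no claim is made there. The correction should be made before the SAP is final.

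**What to change.** In the SAP, define first-time mother as having no child other than the index pregnancy or index infant:

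- pregnant at baseline: no current children;
- enrolled postpartum: no children other than those of the index birth, a multiple birth counting as one.

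Use this one variable both as the covariate and for the primiparous/multiparous strata, and keep prenatal versus postpartum as a separate variable.

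The cost is about one line of text. Number of children is already presupposed by the present rule, and perinatal status is established at eligibility. The one extra need is to recognise a multiple birth, so that a first-time mother of twins is not counted as experienced; if the children's ages are not on the baseline form, a single item would do. The change has no statistical downside and leaves sample size, randomisation and endpoints untouched.

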**Fig. 1 Fig1:**
[figure not shown]
Schedule of screening, enrollment, interventions, and assessments

We anticipate that approximately 24 Judy Center staff will serve as MB-VG facilitators during this study. Each Judy Center staff member who facilitates a MB-VG cohort will be asked to provide informed consent prior to the first group they facilitate. A REDCap link with the informed consent form will be sent to and e-signed by the Judy Center staff/facilitator prior to facilitation. We will recruit the director from each of the 12 participating Judy Centers. Each director will be asked to provide informed consent prior to the completion of the baseline survey and prior to MB-VG implementation at their agency. The informed consent will be sent electronically via a REDCap link.

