### Fidelity assessment of intervention groups

All MB-VG sessions will take place via Zoom, with audio of each session transcribed in Spanish using Zoom’s transcription setting, and then uploaded to a secure online folder accessible only to research staff. Each session will be reviewed to document participant attendance and session length, with a random sample of 20% reviewed in depth to assess fidelity. Fidelity will be assessed using the Revised Cognitive Therapy Rating Scale (CTS-R) [80], previously modified to align with MB. Independent raters will assess fidelity by reviewing audio recordings of intervention sessions and documenting on a 3-point scale the extent to which each topic in a MB-VG session was covered. Adaptations will be assessed by asking facilitators to complete the Modified Adaptation Checklist (MAC) [81, 82] after each cohort they lead; the MAC will assess adaptation in 14 different ways (e.g., skipped topics, modified activities) and for each adaptation reported, whether the adaptation was planned. Adaptations will be explored in semi-structured interviews with facilitators and surveys, guided by Framework for Modification and Adaptations [86],

All Judy Center directors (*n* = 12) will be asked to complete a baseline REDCap survey to assess potential barriers to MB-VG implementation and includes demographic and additional pre-implementation questions assessing readiness, feasibility, acceptability, and appropriateness of the intervention as well as anticipated barriers, as well as a final implementation survey within 1 month after all study cohorts at that site are completed. The final survey will assess director perception of feasibility, acceptability, appropriateness of the intervention, and implementation barriers as well as anticipated barriers to sustainment. All Judy Center directors (*n* = 12) will also complete a semi-structured interview after MB-VG implementation is completed.

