For *Implementation Outcomes*, mean scores of Acceptability of Intervention Measure, Implementation Appropriateness Measure, and Feasibility of Intervention Measure will be calculated for each perinatal participant and facilitator participant to assess MB-VG *acceptability, appropriateness*, and* feasibility*, respectively. We will use descriptive statistics to examine variability in implementation outcomes by respondent type and participant characteristics. We will examine variability in session attendance and utilization of Resource Advocate by participant characteristics. *Fidelity* will be calculated via a mean adherence and competency rating for each rated session with linear mixed models used to evaluate site, participant, and facilitator characteristics’ influence on these outcomes. *Adaptation* will be calculated using descriptive statistics to assess frequency of adaptations with latent class analysis examining whether adaptations group together in underlying patterns across facilitators or Judy Centers. *Cost* implementing MB-VG will be generated by deriving a per-hour salary estimate for each facilitator, Resource Advocate, and pediatrician. When possible, we will obtain actual salaries (see baseline survey for facilitator participants and for director participants); if these salaries are unavailable, we will use state-specific salary estimates based on position title and degree from the Bureau of Labor Statistics for the relevant year. We then will multiply wage rates plus fringe benefits by the time spent engaged in MB training and delivery. Once total costs are calculated, we will calculate a per-organization and per-participant cost of MB-VG. We will aggregate labor and non-labor cost data to measure the cost of implementation from a societal perspective inclusive of organization and participants, as well as reported separately by group. *Maintenance* will be calculated by generating mean scores for the overall SMSS and each of its domains.

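### Latent class analysis of 14 adaptation types across about 24 facilitators or 12 centers is not reliably estimable and should become a descriptive summary

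*Protocol article*

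**What the plan says.** The paragraph on implementation outcomes in the protocol article's section Quantitative analysis plans descriptive frequencies of adaptations, together with "latent class analysis examining whether adaptations group together in underlying patterns across facilitators or Judy Centers". The section Fidelity assessment of intervention groups describes the data source: "the MAC will assess adaptation in 14 different ways", and it records, "for each adaptation reported, whether the adaptation was planned". Collection works by "asking facilitators to complete the Modified Adaptation Checklist (MAC) [81, 82] after each cohort they lead".

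On numbers, the section Participants lists "24 MB-VG facilitators" and 12 center directors. The text after Fig. 1, under Recruitment and consent, repeats both: "We anticipate that approximately 24 Judy Center staff will serve as MB-VG facilitators during this study" and "We will recruit the director from each of the 12 participating Judy Centers". The section Study intervention assigns two co-facilitators to each cohort.

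The article gives no number of classes, no reduction of the 14 types, no rule for choosing a model, and no handling of repeated checklists from one facilitator.

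**The concern.** Latent class analysis estimates, for every class, the probability of each item, plus the class sizes. With 14 items the parameter count soon passes the number of people or centers whose patterns are to be described. The standard model also treats its rows as independent. Checklists filled in repeatedly by one facilitator, or by two facilitators about the same cohort, are not independent.

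At stake is the only model-based analysis planned for Adaptation, an Aim 2 outcome. The section on mixed methods integration merges quantitative and qualitative findings in joint displays to explain variability in implementation and effectiveness. Unstable or false adaptation classes could carry into that explanation.

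**Working it through.** The article states no sample size, power or class number for this analysis, so there is no figure to reproduce.

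**Parameter count.** Assume 14 yes/no items (the response format is not stated) and an unrestricted model. With J items and K classes, free parameters = K × J + (K − 1).
- K = 2: 2 × 14 + 1 = 29
- K = 3: 3 × 14 + 2 = 44
- K = 4: 4 × 14 + 3 = 59
- K = 2 with the 14 planned/unplanned flags added: 2 × 28 + 1 = 57

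The two-class model exceeds 24 facilitators and is 29/12 = 2.4 times the number of centers. To bring it down to about one parameter per unit, the 14 types would have to shrink to 11 for facilitators (2 × 11 + 1 = 23) or 5 for centers (2 × 5 + 1 = 11).

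**Checklist count.** The immediate arm has 150 women. The Discussion mentions 4–5 participants only as the smaller cohort option, so a range of 4 to 12 is assumed. Records = 2 × (150 / cohort size, rounded up).

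| Cohort size (assumed) | Cohorts | Checklists |
|---|---|---|
| 4 | 38 | 76 |
| 5 | 30 | 60 |
| 8 | 19 | 38 |
| 10 | 15 | 30 |
| 12 | 13 | 26 |

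Most of these counts exceed 29. However, they come from about 24 people, with two reports on each cohort. If delayed-arm cohorts also complete the checklist, which is not stated, the counts can double (52 to 152 if all 150 control women take part), with the same dependence.

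**Simulation.** Each scenario used 100 datasets with 14 binary items and two equal classes, fitted by EM with several random starts. Half the items were more common in one class and half in the other. The two figures in each scenario are those item probabilities; the null has no classes and all probabilities 0.3.

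| Units | Scenario | BIC picks 2 classes | AIC picks 2 classes | Classification accuracy |
|---|---|---|---|---|
| 12 | null | 4% | 19% | – |
| 12 | 0.5 vs 0.2 | 12% | 49% | 0.78 |
| 12 | 0.7 vs 0.2 | 95% | 99% | 0.95 |
| 24 | null | 1% | 37% | – |
| 24 | 0.5 vs 0.2 | 10% | 74% | 0.79 |
| 24 | 0.7 vs 0.2 | 95% | 100% | 0.95 |
| 60 | null | 0% | 34% | – |
| 60 | 0.5 vs 0.2 | 21% | 97% | 0.82 |
| 60 | 0.7 vs 0.2 | 100% | 100% | 0.97 |

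Under the null, the mean entropy of the two-class fit was 0.94 with 24 units and 0.99 with 12, so false classes look well separated. In those fits 15% and 29% of item probabilities sat on the boundary. The 60-unit rows treat records as independent, which flatters the per-cohort checklists; moderate classes were still missed by BIC in 79% of datasets.

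**A plausible alternative to classes.** Suppose there are no classes, and facilitators differ only in an overall tendency to adapt (log-odds SD 1 around a base rate of 0.3, both assumed). With one checklist each from 24 facilitators, BIC chose more than one class in 42% to 47% of datasets over repeat runs. With three dependent checklists each it did so in 75% to 78%. Repeated rows made false classes more likely.

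**The case against.** A reader might infer from 29 parameters against 24 or 12 units that the model is unidentified, that it cannot yield interpretable classes, or that any classes would only reflect starting values. The documents do not support that. Identification depends on parameters against response cells, here 29 against 2^14 − 1 = 16,383, and 24 units supply 24 × 14 = 336 item responses. Two strongly separated classes were recovered in 95% of datasets, and BIC rarely erred under the plain null. In one run with 24 units, 81% of starts reached the best solution for strong classes, against 38% for moderate ones.

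The unit of analysis is also open. The reference to facilitators or centers may say where patterns are compared and not what forms a row; with per-cohort records the raw count can pass 29. That stands as far as the count goes, but nesting in the same facilitators remains. No firm upper limit on records can be given, because checklist use in delayed-arm cohorts is not stated.

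Item collapsing, priors, a multilevel model or a selection rule may be set out in an analysis plan that is not shown, and their absence here is no fault. The point is that the article already names the method, the 14 types and the numbers of facilitators and centers, and that combination is fragile.

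Finally, the frequencies, planned flags and interviews are already in the plan, and hierarchical clustering would be unstable too. Both are fair, and the fix allows for them.

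**Conclusion.** The point holds in this limited form. A latent class analysis of 14 adaptation types over about 24 facilitators or 12 centers is not reliably estimable. It would find very strongly separated classes, usually miss moderate ones under BIC (about 10% found with 24 units), and report clean-looking false classes in a substantial share of cases under AIC (37%) or when facilitators simply differ in how much they adapt (42% to 47% under BIC, more with repeated checklists).

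This rests on binary scoring, all 14 types entered separately, an unrestricted model without adjustment for clustering, equal class sizes, and the assumed cohort sizes and spread between facilitators. The center count may in effect be lower than 12, since some sites may only refer participants.

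The consequence is small: one Aim 2 sub-analysis, with no bearing on the effectiveness endpoints.

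**What to change.** In the implementation outcomes paragraph of Quantitative analysis, replace the latent class analysis with frequencies for each adaptation type, split by planned and unplanned, and a table of which types occur together, shown by facilitator and center. Label this descriptive and link it to the facilitator interviews that already explore adaptations. If a clustering display is wanted, label it exploratory, since it is also unstable at this sample size.

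The cost is a change of wording and the loss of model-based classes. No data collection changes.
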